### Inclusion And Exclusion Criteria

Inclusion criteria are:

Adult patients (>18 years)

Clinical (pain, fever > 37.5°C, WBC > 10.000/microL), and ultrasound evidence of cholecystitis

ASA I-III patients

Informed consent

Less than 72 h from the onset

Exclusion criteria

Informed consent refusal

Choledocholithiasis

Generalized peritonitis

Previous abdominal surgical procedures

Patients with an intra-operative findings of different pathology will be excluded from the study

Apache II score > 10

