#### Randomization

The randomization will be obtained through computer-generated schedule. The result of this randomization will be sealed in numbered envelopes. After cholecystitis diagnosis if the patient fulfils the inclusion criteria the responsible surgeon will ask the patient to partecipate to the study. If the patient agree, he/she will sign the informed consent. After patient's consent the randomization will be carried out. The responsible surgeon will record the patient name (and number). All eligible patients will be recorded.

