#### Intervention

Preoperative data collected will include patient demographics and comorbid conditions (genitourinary, cardiac, pulmonary, gastrointestinal, renal, or rheumatologic) and a detailed history of symptom onset.

The procedure was performed by a surgeon that had performed at least 50 LCs.

On admission, the patients were started on cefotaxime, 2 g IV every 12 h, which was continued postoperatively according to NNISS score [9].

The standard four-trocar operative technique is used for LC for acute cholecystitis.

When the gallbladder is distended it will be first aspirated. To allow a good hold on the gallbladder larger graspers will be inserted through a 5 mm right lower port. The cystic artery and duct are clip-ligated. The gallbladder and intraperitoneal "dropped" stones are collected in an endoscopic bag and extracted through the umbilical cannula site, which can be extended. A closed system suction drain is left. Fascial closure is attempted only at the umbilical cannula site. The skin at all the cannula sites are closed with staples.

Laparotomic procedure is carried out with an about 8 cm right subcostal incision and the traditional surgical technique with a closed system suction drain left in situ.

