#### Data Collection

Patients' data sheets are generated containing demographic data and preoperative, operative, and postoperative information.

Pre-operative notes concern the history of gallbladder stones, the presence of associated diseases (cardiac, hypertension, diabetes, malignancy), duration of gallbladder complaints (as an indication for the onset of the disease), finding of a palpable gallbladder, temperature, and laboratory results of WBC count, serum bilirubin, gamma GT, PCR, IL-6 and alkaline phosphatase. Ultrasound findings are also reported.

Operative data of concern are macroscopic findings (of acute cholecystitis, gangrenous cholecystitis, hydrops, and empyema of the gallbladder), the presence of small stones (< 1 cm diameter) or large bile stones (> 1 cm diameter), information regarding perforation of the gallbladder and intraperitoneally "lost" stones, reasons for conversion, and duration of surgery. Postoperative notes of interest included the use of nasogastric tubes and drains, the amount of analgesics used, (evaluation of pain with VAS score), complications, and length of hospital stay.

Complications are classified as surgical infections (wound infection, subphrenic or subhepatic abscess); noninfectious surgical problems (e.g., bile duct injury, hemorrhage); remote infections (urinary or respiratory); and miscellaneous problems (e.g., atelectasis, deep vein thrombosis, AMI, CVA, etc). The collected information are entered into a database as either continuous or categorical variables for statistical analysis. Following the operative procedure, a large sterile dressing will be applied to cover the entire abdomen.

A second surgical team, aware of the operative findings but not the surgical access approach, then will assume the care of the patient. Postoperative care and ability to be discharged from the hospital will be determined by the second surgical team. This second surgical team will be blinded to the surgical approach. The primary operative team will be in every moment available for emergent consultation or evaluation of the wound.

In the pre-anaesthetic holding area, baseline pain will be investigated at rest and on coughing using a pain-rating scale systems: a 100-mm visual analogue scales (VAS) (0 = minimal and 100 = maximal).

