### Primary Endpoints

The aim of the study is to compare the results of early laparoscopic and laparotomic cholecystectomy for acute cholecystitis in terms of morbidity, mortality, conversion rate, operation time, hospital stay, postoperative pain, return to normal activity and aesthetic result.

The primary endpoints of our study will be:

To evaluate the value of laparoscopic cholecystectomy to reduce hospital stay

To evaluate the value of laparoscopic cholecystectomy to reduce postoperative pain

To evaluate the conversion rate

The onset of any other complications will be recorded intraoperatively, postoperatively, at discharge, at 7-days, 1-month and 6-months.

All the above mentioned data will be recorded in the Case Report Form and later stored in computer database. At the end of the study the final statistical examination will be carried out.

An interim statistical examination of the data will be done every 3 months during the period of patients' inclusion in the study. Then at the end of every completed follow-up period (1-month, 6-months).

The statistical analysis will be carried out using Epi Info 2000, Version 1.1 software package (Dean AG, Arner TG, Sangam S, Sunki GG, Friedman R, Lantinga M, Zubieta JC, Sullivan KM, Smith DC. Epi Info 2000, a database and statistics program for public health professionals for use on Windows 95, 98, NT, and 2000 computers; Centers for Disease Control and Prevention, Atlanta, Georgia, USA, 2000)

No incentives are planned for the patients regarding the operation or the follow-up.

The study will take approximately 6 months – 1 year for the inclusion period. According to the number of AC menaged monthly in all Centers, the duration of the inclusion period can be approximately of 1 year to reach the number of about 144 enrolled patients.

An interim report is planned at the end of any completed follow-up period.

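### Excluding randomised patients for a different pathology found at operation can bias the hospital-stay comparison if detection or labelling differs by arm

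*Protocol article*

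**What the plan says.** The order of events is fixed in the Randomization section of the protocol article: "After patient's consent the randomization will be carried out". Because the allocation decides the access route, this precedes surgery. Under Inclusion And Exclusion Criteria, the list of exclusions contains one that can be met only later: "Patients with an intra-operative findings of different pathology will be excluded from the study". The removal is from the study as a whole, not from one analysis set.

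The Intervention section describes a four-trocar technique for the laparoscopic arm (LC). For the open arm (LTC) it says: "Laparotomic procedure is carried out with an about 8 cm right subcostal incision".

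The Data Collection section limits knowledge of the approach after the operation: "A second surgical team, aware of the operative findings but not the surgical access approach, then will assume the care of the patient". It also describes a blinded pain assessor. Neither provision covers the team that operates.

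The same section lists what is recorded at operation, including macroscopic findings from acute cholecystitis to empyema, gallbladder perforation and reasons for conversion. It does not say which findings count as a different pathology.

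The Randomization section adds: "All eligible patients will be recorded". No section says that patients excluded at operation are followed or analysed. The primary endpoints are hospital stay, postoperative pain and conversion rate.

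**The concern.** Randomisation protects the comparison only for the set of patients who were randomised. A rule that drops patients after allocation keeps that protection only if it works the same way in both arms.

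Three features leave that unsecured here. The operating team cannot be blind to the approach. The two routes expose the abdomen differently, so another disease may be seen more often through one than the other. And the deciding term is left to judgement.

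If exclusion then differs between arms, and the excluded patients would have had unusually long or short stays, the observed difference in hospital stay is partly an artefact. Pain could be affected in the same way if the excluded patients differ in pain, though the documents give nothing from which to gauge this. Conversion occurs only in the LC arm, so no contrast between arms is at risk there, but the reported rate depends on who has been removed.

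**Working it through.** **1. The plan's own figure.** The Statistics section gives 72 per group, 95% confidence and 80% power, and a hospital-stay assumption read here as a 2-day difference (the wording is ambiguous). It gives no standard deviation (SD), so 72 cannot be reproduced from stated inputs. Solving n = 2(1.96 + 0.84)²·SD²/δ² for n = 72 and δ = 2, two-sided, gives SD = 2 × √36 / 2.80 = 4.28 days. This value is back-solved and serves only as a scale for what follows.

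**2. Bias in hospital stay.** All inputs in this step are assumptions, because the documents give neither an exclusion rate nor the stay of excluded patients. Suppose there is no true effect, a share q of patients in each arm has another pathology and stays D days longer, and a share e of the arm is excluded, all of them from that subgroup. Relative to the other patients, the mean stay of those who remain is (q − e)·D/(1 − e). The spurious difference is the LC value minus the LTC value.

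| q | D (days) | e in LC | e in LTC | Spurious LC − LTC (days) |
|---|---|---|---|---|
| 10% | 4 | 5% | 5% | 0.00 |
| 10% | 4 | 5% | 2% | −0.12 |
| 10% | 4 | 8% | 3% | −0.20 |
| 10% | 6 | 8% | 3% | −0.30 |
| 10% | 6 | 3% | 8% | +0.30 |

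For the fourth row: 0.02 × 6/0.92 = 0.13; 0.07 × 6/0.97 = 0.43; difference −0.30. The last row swaps the arms and reverses the sign. So would excluded patients with shorter stays.

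A bias of 0.30 day is 0.30/2 = 15% of the 2-day difference. The standard error is 4.28 × √(2/72) = 0.71 day, so such a bias would raise the two-sided error from 5% to about 7%. A harsher set of assumptions (8 days longer, 10% against 5% excluded) gives 0.42 day and about 9%.

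**3. Conversion rate.** Take 25 conversions in 72 LC patients, 34.7%, close to the upper figure of 35% in the Introduction. Removing one converted patient gives 24/71 = 33.8%; removing five gives 20/67 = 29.9%. Removing five unconverted patients instead gives 25/67 = 37.3%. The rate moves either way, depending on who is removed.

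**4. Power under exclusion and under retention**, with δ = 2 and SD 4.28:
- Excluding 5% of each arm leaves 68.4 per arm and 78.0% power. Excluding 10% leaves 64.8 and 75.7%.
- Keeping 5% who stay 5 days longer, with 4.28 taken as the SD of the rest, gives variance 18.34 + 0.05 × 0.95 × 25 = 19.53, SD 4.42, and power of about 77.5% at 72 per arm.
- If those patients gain nothing from LC, the difference falls to 0.95 × 2 = 1.9 days and power, at the same SD, to about 73%.

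Retention therefore does not gain power over exclusion.

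**The case against.** The strongest reply is that a different disease is present before randomisation. Dropping patients who never had the condition under study is then harmless, provided it is done alike in both arms; the first row of the table shows zero bias in that case. This stands, and it limits the point to a risk rather than a demonstrated bias. It does not remove the risk, because nothing in the article secures equal detection or blind judgement.

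A reader might go further and infer that hard laparoscopic cases would be converted, relabelled as another pathology and dropped, so that the rule favours LC. The documents do not support this. Data Collection treats gangrene, empyema, perforation and reasons for conversion as ordinary in-study data, and conversion is itself an endpoint. The natural reading of the criterion is a wrong diagnosis, not a difficult cholecystitis. Nothing shows that more patients would be excluded from LC, or that excluded patients stay longer.

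A reader might also argue that the exclusions erode the 80% power and that retention restores it. Step 4 of the working shows otherwise.

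Two further replies carry part of the way. Eligible patients are to be recorded, so excluded patients need not vanish from the report; but recording does not keep them in the comparison. And a fuller protocol or analysis plan may define the term. The removal from the study, however, is stated in this article, and an analysis plan could not reverse it without contradicting it.

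**Conclusion.** The point holds as a conditional one. The article states a rule that removes randomised patients on an undefined finding, made after allocation by a team that necessarily knows the arm and works through a different access route in each arm. That the operating team knows the arm is inferred from the design, but it is unavoidable.

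Bias in hospital stay, and possibly in pain, follows only if detection or labelling differs by arm and is related to prognosis. Direction and size cannot be derived from the documents. On the assumptions tabulated, the size is 0 to about 0.3 day in either direction, and larger only under harsher assumptions. For conversion, the effect is a changed LC rate and denominator, not a biased contrast. It would be too strong to say that the rule certainly breaks the randomised comparison or that it favours LC.

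**What to change.** Delete the line from the exclusion criteria. State that every randomised patient is followed for all endpoints and analysed in the allocated arm, and that this is the primary analysis. Report the intra-operative diagnoses by arm.

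Leave out patients with other pathology only in a sensitivity analysis. Define the term in advance and have it applied to the recorded operative findings by someone who does not know the arm. The plan already passes operative findings to a second team without the access route, so this looks feasible, but entries that reveal the route, such as reasons for conversion, must be masked. Pathology reports are not among the listed data, so the definition should not depend on them unless they are added.

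The cost is a short change of text, follow-up of a few more patients and a small blinded classification task. The statistical price is some dilution and added variance from patients without cholecystitis, as in step 4 of the working. That price is worth paying for a comparison that rests on the randomised groups. The change must be made before enrolment, because data on patients who are dropped and not followed cannot be recovered later.

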#### Intervention

Preoperative data collected will include patient demographics and comorbid conditions (genitourinary, cardiac, pulmonary, gastrointestinal, renal, or rheumatologic) and a detailed history of symptom onset.

The procedure was performed by a surgeon that had performed at least 50 LCs.

On admission, the patients were started on cefotaxime, 2 g IV every 12 h, which was continued postoperatively according to NNISS score [9].

The standard four-trocar operative technique is used for LC for acute cholecystitis.

When the gallbladder is distended it will be first aspirated. To allow a good hold on the gallbladder larger graspers will be inserted through a 5 mm right lower port. The cystic artery and duct are clip-ligated. The gallbladder and intraperitoneal "dropped" stones are collected in an endoscopic bag and extracted through the umbilical cannula site, which can be extended. A closed system suction drain is left. Fascial closure is attempted only at the umbilical cannula site. The skin at all the cannula sites are closed with staples.

Laparotomic procedure is carried out with an about 8 cm right subcostal incision and the traditional surgical technique with a closed system suction drain left in situ.

#### Data Collection

Patients' data sheets are generated containing demographic data and preoperative, operative, and postoperative information.

Pre-operative notes concern the history of gallbladder stones, the presence of associated diseases (cardiac, hypertension, diabetes, malignancy), duration of gallbladder complaints (as an indication for the onset of the disease), finding of a palpable gallbladder, temperature, and laboratory results of WBC count, serum bilirubin, gamma GT, PCR, IL-6 and alkaline phosphatase. Ultrasound findings are also reported.

Operative data of concern are macroscopic findings (of acute cholecystitis, gangrenous cholecystitis, hydrops, and empyema of the gallbladder), the presence of small stones (< 1 cm diameter) or large bile stones (> 1 cm diameter), information regarding perforation of the gallbladder and intraperitoneally "lost" stones, reasons for conversion, and duration of surgery. Postoperative notes of interest included the use of nasogastric tubes and drains, the amount of analgesics used, (evaluation of pain with VAS score), complications, and length of hospital stay.

Complications are classified as surgical infections (wound infection, subphrenic or subhepatic abscess); noninfectious surgical problems (e.g., bile duct injury, hemorrhage); remote infections (urinary or respiratory); and miscellaneous problems (e.g., atelectasis, deep vein thrombosis, AMI, CVA, etc). The collected information are entered into a database as either continuous or categorical variables for statistical analysis. Following the operative procedure, a large sterile dressing will be applied to cover the entire abdomen.

A second surgical team, aware of the operative findings but not the surgical access approach, then will assume the care of the patient. Postoperative care and ability to be discharged from the hospital will be determined by the second surgical team. This second surgical team will be blinded to the surgical approach. The primary operative team will be in every moment available for emergent consultation or evaluation of the wound.

In the pre-anaesthetic holding area, baseline pain will be investigated at rest and on coughing using a pain-rating scale systems: a 100-mm visual analogue scales (VAS) (0 = minimal and 100 = maximal).

An investigator blinded to the study operation performed, will evaluate postoperative pain intensity on returning to the Surgical Ward (zero time), and after 12 and 24 hours (± 3 hours). The three hours of tolerance (before or after the precise time of control) will be used in order to avoid to awake the patients during the night. But during the day time, if asleep, the patient will be awakened for the pain test. At these timed intervals, the following variable will be recorded: VAS for pain at rest, and on coughing; if, at rest, VAS is more than 3, the patient will be given intravenous 30 mg ketorolac. The pain tests will be also performed whenever the patient ask for additional analgesia between the timed controls and parenteral analgesics will be administered accordingly. Every time the patient undergoes the pain test, he will be asked about the location of pain (in the surgical wound, far from the wound, everywhere or does not know). As soon as patients will begin to drink fluid instead of ketorolac 30 mg iv, they will be offered nimesulide 100 mg 1 tab orally prn (max 2 tabs daily). Orally administered analgesics will be continued in preference to parenterally administered analgesics if they will be efficacious. After discharge, the patients will be offered nimesulide 100 mg 1 tab orally prn (max 2 tabs daily). Also parenteral and oral analgesic drug requirements will be recorded and analyzed as a measure of postoperative pain. Furthermore the patient satisfaction with the analgesia provided (using a scale of poor, satisfactory, good, or excellent) will be recorded before discharge and after 7 days.

Patient discharge will be based on good medical practice criteria: 1) apyrexia 2) absence of diseases requiring hospitalisation 3) return of bowel function 4) patient's compliance.

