# The ACTIVE (Acute Cholecystitis Trial Invasive Versus Endoscopic) study: Multicenter randomized, double-blind, controlled trial of laparoscopic (LC) versus open (LTC) surgery for acute cholecystitis (AC) in adults

**DOI:** 10.1186/1745-6215-9-1

**Published:** 2008-01-10

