**Trial Registration:**

TRIAL REGISTRATION NUMBER ISRCTN27929536 – The ACTIVE (Acute Cholecystitis Trial Invasive Versus Endoscopic) study. A multicentre randomised, double-blind, controlled trial of laparoscopic versus open surgery for acute cholecystitis in adults.

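### The trial is called double-blind without limit, but the blinding described stops at in-hospital care, discharge and 24-hour pain and cannot cover wound infection, aesthetic result or later patient-reported outcomes

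*Protocol article*

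**What the plan says.** The title describes a "Multicenter randomized, double-blind, controlled trial of laparoscopic (LC) versus open (LTC) surgery for acute cholecystitis (AC) in adults". The registration text in the abstract repeats the label: "A multicentre randomised, double-blind, controlled trial of laparoscopic versus open surgery for acute cholecystitis in adults". Neither limits it to particular outcomes or times. The abstract and the Introduction also fault earlier studies for not being double blinded, so blinding is put forward as an advantage of this trial.

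The mechanism is under Data Collection. After the operation "a large sterile dressing will be applied to cover the entire abdomen". A second team that does not know the approach then takes over: "Postoperative care and ability to be discharged from the hospital will be determined by the second surgical team". A blinded investigator measures pain on return to the ward and at 12 and 24 hours. On the wound, the section says: "The primary operative team will be in every moment available for emergent consultation or evaluation of the wound".

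The outcomes reach further than these measures:

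- Data Collection: "Complications are classified as surgical infections (wound infection, subphrenic or subhepatic abscess", followed by other categories.
- Data Collection, on satisfaction with analgesia: "will be recorded before discharge and after 7 days".
- Primary Endpoints: "The onset of any other complications will be recorded intraoperatively, postoperatively, at discharge, at 7-days, 1-month and 6-months".
- The aim sentence under Primary Endpoints also lists morbidity, return to normal activity and aesthetic result.

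**The concern.** The blind depends on the incision staying covered. The second team cannot inspect the wound without learning the approach. That is presumably why the operating team, who know it already, are kept on call for the wound. Yet wound infection is part of the morbidity comparison, is the complication most closely tied to the incision, and leaves room for judgement. Aesthetic result is a judgement about the scar itself.

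If these outcomes are reported under an unqualified double-blind label, readers will give them the protection that stay and early pain have. A difference in wound infection, satisfaction, return to activity or appearance could then be taken as blinded evidence when knowledge of the approach may have created or enlarged it.

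**Working it through.** **Step 1: set the claim against the mechanism.** The Intervention section gives a four-trocar technique with stapled cannula sites for the laparoscopic arm and a right subcostal incision of about 8 cm for the open arm. Uncovered, the two cannot be confused.

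| Outcome | Blinding described | Can it be blind? |
|---|---|---|
| Hospital stay | Second team, blinded, decides discharge | Yes, as described |
| Pain to 24 h | Blinded investigator, dressing in place | Yes, as described |
| In-hospital analgesia | Follows the pain tests and the blinded team's care | Yes, as described |
| Wound infection | None; only the operators are named for the wound | No; the incision must be seen |
| Aesthetic result | None | No; the scar is what is judged |
| Satisfaction after 7 days, return to activity | None | Not for the patient once the dressing is off |
| Other complications, 7 days to 6 months | None | Possibly; masked assessment is not excluded |

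Four compared outcomes therefore lie outside the blind by their nature: wound infection, aesthetic result, 7-day satisfaction and return to activity. For the last row the article is only silent.

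**Step 2: what unblinded wound calls could do.** The article gives no infection rate and no estimate of misclassification, so this step is illustrative.

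- From the Statistics section: n = 72 per arm, significance at 0.05, Fisher's exact test or chi-square as appropriate.
- Assumed: true infection rate p = 0.08 in both arms, and equivocal wounds also called infected in a further e = 0, 0.04 or 0.08 of patients in one arm only.

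The chance of a significant result is the sum, over all pairs (a, b) with test p-value at or below 0.05, of Bin(a; 72, p) × Bin(b; 72, p + e).

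| Recorded rates | Expected counts (72 × rate) | Fisher | Uncorrected chi-square |
|---|---|---|---|
| 8% v 8% | 5.76 v 5.76 | 0.022 | 0.052 |
| 8% v 12% | 5.76 v 8.64 | 0.077 | 0.126 |
| 8% v 16% | 5.76 v 11.52 | 0.237 | 0.315 |

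Both tests are shown because the Statistics section allows either, and expected counts just above 5 do not settle the choice. The low 2% starting value reflects Fisher's conservatism. From the unbiased to the worst case the ratio is 0.237 / 0.022 ≈ 11 with Fisher and 0.315 / 0.052 ≈ 6 with chi-square.

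**Step 3: sensitivity to the assumed rate.** I repeated the Fisher sum for true rates of 4%, 6%, 8% and 10%. With no extra calls it gives 1% to 3%, with 4 points 7% to 8%, and with 8 points 21% to 31%. The pattern does not depend on choosing 8%.

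The plan's sample size of 144 does not bear on the blinding question.

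**The case against.** **The operators are on standby, not adjudicating.** The wound sentence makes them available. It does not say that they diagnose, classify or record wound infection as an outcome, and the second team has charge of care. This stands: a reader might infer that surgeons score their own wounds for the trial, and the text does not go that far. What remains is that no other wound evaluator is named and that anyone who inspects the wound learns the approach.

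**Silence about follow-up is not a defect in a condensed article.** It does not say when the dressing comes off, who assesses at 7 days, 1 month or 6 months, or whether that person is masked. A reader might infer that every comparison from day 7 is open-label. The article does not support this: remote infections, thrombosis, infarction or stroke could be assessed by someone who never sees the abdomen. The objection does not rescue wound infection, aesthetic result or later patient reports, because no fuller protocol could hide port sites from a subcostal scar or keep patients unaware of their own incision.

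**The primary endpoints are untouched.** Stay has a blinded decision-maker, pain to 24 hours has a blinded assessor, and conversion arises only in the laparoscopic arm. This stands and limits the weight of the point.

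**The magnitude is assumed.** The infection rate, the extra calls and their confinement to one arm have no source in the article, which states no operator expectation about wound infection. This stands; the figures show what such a bias could do, not that it occurs.

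**Visible scars are inherent in the comparison.** True. That is a reason to narrow the claim, since the design cannot be made to meet it.

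**Conclusion.** The concern holds in a limited form. The double-blind label is unqualified, while the blinding described covers in-hospital care, the discharge decision and pain to 24 hours. Wound infection and aesthetic result cannot be blinded to approach, and 7-day satisfaction and return to activity cannot be patient-blind once the dressing is off. That rests on the incisions described and on the ordinary inference that patients see their own wounds. For other complications from day 7 to 6 months one can say only that no masking is described.

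If 4 or 8 points of extra infection calls fell in one arm at a true rate of 8%, the false-positive chance would be 8% or 24% with Fisher (2% without bias), or 13% or 31% with uncorrected chi-square (5% without bias). Rates, size and direction are all assumptions. The point should be acted on because it changes what the trial may conclude on these outcomes, but it does not threaten the primary comparisons of stay and early pain.

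**What to change.** 1. **Limit the claim.** In the title, registration text and report, confine double-blind to hospital stay, in-hospital VAS and in-hospital analgesia. Report wound infection, aesthetic result, return to activity and post-discharge satisfaction as not blinded, and word conclusions on them accordingly.

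2. **Fix the evidence for wound infection.** Under Data Collection, count a wound infection in the morbidity comparison only on prespecified, documented objective evidence, for example pus or a positive culture. Apply it identically in both arms, whoever inspects the wound. Record on the case report form whether the assessor knew the approach. This concerns what is counted, not how wounds are managed.

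Moving wound assessment to the second team at 7 days and 1 month is not proposed. That team would lose the blind on seeing the incision, and the article describes it for in-hospital care only, so extra staff might be needed.

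The cost is a few lines of protocol and case report form items for the evidence and the assessor's knowledge of the approach. The downsides are a narrower blinding claim and possibly fewer wound infections counted. The criterion reduces the room for judgement without restoring the blind, since the decision to take a culture still lies with someone who can see the wound.

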### Statistics

Sample size has been calculated to reach a confidence level of 95% with a power of 80%.

A sample size of 144 patients is calculated supposing that the hospital stay for LC is shorter than 2 days. The sample size will be 72 patients for each group (144 patients for the whole study).

For comparison of the two groups, chi-square analysis and Fisher's exact test are used when appropriate for qualitative data, and the Student t-test (for normal variables) or the Mann Whitney U-test (for nonnormal variables) for quantitative data. For multivariate analysis the stepwise logistic regression is applied. A probability of 0.05 or less is accepted as statistically significant.

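### Pain is a listed primary endpoint with its own baseline VAS, but the tests named for quantitative data take no covariate, so available precision may be lost (not validity)

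*Protocol article*

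**What the plan says.** The Data Collection section of the protocol article provides for a preoperative reading: "baseline pain will be investigated at rest and on coughing using a pain-rating scale systems", on a 100-mm VAS. After surgery a blinded investigator assesses pain on arrival at the ward, at 12 hours and at 24 hours, and "the following variable will be recorded: VAS for pain at rest, and on coughing". Baseline and outcome are therefore the same two quantities on the same scale.

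The Primary Endpoints section lists three items, one of which is "To evaluate the value of laparoscopic cholecystectomy to reduce postoperative pain".

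The Statistics section chooses tests by type of variable. For continuous outcomes it names "the Student t-test (for normal variables) or the Mann Whitney U-test (for nonnormal variables) for quantitative data". The one multivariable method is given in the sentence "For multivariate analysis the stepwise logistic regression is applied". The significance rule is "A probability of 0.05 or less is accepted as statistically significant". VAS is not mentioned in that section, and the article nowhere assigns the baseline reading a part in the comparison of pain.

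**The concern.** A baseline measured on the outcome's own scale is usually the first covariate one would want in a model for that outcome. Here it is collected for a primary endpoint, and the tests then named cannot use it as a covariate. The multivariable method named does not fill the gap: logistic regression is for a binary outcome, not a 0 to 100 score, and stepwise selection lets the data choose the covariates.

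Two things are at stake. First, variation in postoperative pain that preoperative pain could explain stays in the error term. Second, with 72 patients per arm, the arms can differ by chance in preoperative pain, and an unadjusted comparison carries part of that difference into the result. Pain is an entry criterion and patients may be up to 72 hours from onset, so some spread at baseline is plausible. The sample size rests on hospital stay alone, so power for pain is unknown.

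**Working it through.** **The plan's own figure.** The Statistics section gives 72 per arm, 95% confidence and 80% power, based on hospital stay. Reading it as a 2-day difference, two-sided, the implied SD is 2 × √(72/2) / (1.960 + 0.842) = 12 / 2.802 ≈ 4.28 days. No SD is stated, so the 144 can be neither confirmed nor refuted. The present point uses only the 72 per arm.

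**Inputs.** n = 72 per arm and alpha 0.05 are from Statistics; sidedness is not stated and two-sided is assumed. The article gives no effect size or SD for pain and no correlation r. I take r from 0 to 0.5 and, for illustration only, an effect that gives the unadjusted t-test 80% power:

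d = (1.960 + 0.842) × √(2/72) = 0.467 SD.

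**Precision.** Adjusting for baseline multiplies the residual variance by 1 − r². Hence:

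- equivalent unadjusted patients per arm = 72 / (1 − r²)
- power = Φ(2.802 / √(1 − r²) − 1.960)

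| r (assumed) | Variance ratio | Equivalent n per arm | Power with ANCOVA |
|---|---|---|---|
| 0 | 1.00 | 72 | 80.0% |
| 0.1 | 0.99 | 72.7 | 80.4% |
| 0.2 | 0.96 | 75.0 | 81.6% |
| 0.3 | 0.91 | 79.1 | 83.6% |
| 0.4 | 0.84 | 85.7 | 86.4% |
| 0.5 | 0.75 | 96.0 | 89.9% |

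**Check by simulation** (4000 normal data sets per r, 72 per arm, d = 0.467). The last column is a t-test on change from baseline, with equal SDs before and after surgery.

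| r | t-test | Mann-Whitney | ANCOVA | Change score |
|---|---|---|---|---|
| 0 | 0.79 | 0.77 | 0.79 | 0.49 |
| 0.2 | 0.80 | 0.78 | 0.81 | 0.61 |
| 0.3 | 0.79 | 0.77 | 0.83 | 0.64 |
| 0.5 | 0.80 | 0.78 | 0.89 | 0.79 |

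The ANCOVA column agrees with the formula. At r = 0 the covariate costs essentially nothing.

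**Change from baseline.** Relative to the raw score, the change score has variance 2(1 − r): 1.6 at r = 0.2, 1.4 at 0.3 and 1.0 at 0.5. It is therefore less precise than the plain t-test whenever r is below 0.5.

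**Chance imbalance.** The baseline difference between arms has standard error √(2/72) = 0.167 SD. With equal SDs, an imbalance of that size moves the unadjusted pain difference by r × 0.167: 0.017 SD at r = 0.1, 0.050 at 0.3 and 0.083 at 0.5, against the reference effect of 0.467. ANCOVA removes this shift.

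**The case against.** **The text does not say how VAS will be analysed.** A reader might infer that raw postoperative scores will be tested separately at each time and that the baseline will never be used. The article does not say so. Statistics lists tests by type of variable, and Data Collection gives measurement times, not analysis variables. A t-test on change from baseline, or on a summary per patient, fits the same words. This stands, and it also removes any firm claim that the repeated measurements will be mishandled. It does not rescue the plan: the tests named still take no covariate, and change scores do worse than the plain t-test when r is below 0.5.

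**A condensed article may leave covariates to a SAP.** True of covariate lists in general. The point here is narrower: the article does state a method for quantitative outcomes, and a better one is available with data already collected.

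**Nothing is invalid.** This stands. Randomisation makes the unadjusted tests valid, and a reader who infers a biased pain result goes beyond the documents.

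**The gain may be small.** This stands too. Baseline pain is that of the inflamed gallbladder; later pain follows its removal through an access that differs by arm, and analgesia triggered by the resting VAS or given on request alters later scores. A low r is plausible, and at r of 0.3 or less the gain is under 4 percentage points of power. The 80% starting point is itself hypothetical.

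**Conclusion.** The point holds as a recommendation on efficiency. The tests stated for quantitative data cannot use, as a covariate, the baseline VAS that the protocol collects for a listed primary endpoint. The cost is possible loss of precision and chance imbalance left unaddressed; it is not bias or a wrong type I error rate.

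For r from 0.1 to 0.5, ANCOVA lowers the variance by 1% to 25%, and a hypothetical 80% power becomes about 80% to 90%. The gain is minor unless r is about 0.4 or more. These figures rest on an assumed correlation, a two-sided 5% test, an illustrative effect of 0.467 SD and approximately normal scores. They illustrate the trade-off and do not estimate this trial's power for pain. What supports the change despite the uncertainty is the asymmetry: some gain if r is moderate, essentially no loss if it is zero.

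**What to change.** Add to the Statistics section that postoperative VAS will be compared between arms by ANCOVA with treatment and the matching baseline VAS (rest for rest, cough for cough) as a prespecified covariate, and that the adjusted difference will be reported with its 95% CI. State that a rank-based or robust version will be used if the scores are skewed, and keep the Mann-Whitney test as a sensitivity check.

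Optional extension: one repeated-measures model over 0, 12 and 24 hours with the same baseline covariate. The main fix does not depend on it.

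Cost: a change of analysis wording, made before the pain data are compared by arm. No new measurements, visits or patients are needed. Confirm that the software named under Primary Endpoints can fit the chosen model, or name another package.
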